Abdomen is distended but not tense	1
Abdomen is distended and tense, responsive to gastric suction/rectal stimulation	2
Abdomen is distended and tense, not responsive to gastric detension/rectal stimulation	3

Data on respiratory support, nutrition, growth, and overall clinical status will be collected from enrollment to discharge. According to an intention-to-treat model, each patient will be monitored whatever the occurring clinical events, including the failure of the modality of respiratory support assigned at enrollment. Death or transfer to another hospital before reaching FEF will be the only reasons for a patient to drop the study.

All data to be collected will be obtained from the clinical records. Data will be recorded on a common database available on the ENTARES website and specifically designed for this study. Access to the database will be password protected, and data will be entered by the local principal investigator. Participants will be identified by trial number only.

All data recorded throughout the study period are listed in Table 3.

**Table 3 Tab3:** Data recorded during the study period

Ventilation/respiration parameters^a^	
– Respiratory support technique – PEEP/CPAP (cmH_2_O) – Peak inspiratory pressure (PIP, cmH_2_O) – Flow (L/min) – FiO_2_ (%) – Respiratory rate (acts/min) – Transcutaneous O_2_ blood saturation (SatO_2 TC_ %) – Capillary/arterial blood gas test – Episodes of apnea (> 20 s or > 5 s if followed by bradycardia/desaturation), bradycardia (Heart rate ≤ 80 bpm) and desaturation (SatO_2 TC_ ≤ 80%)/day – Silverman score	
Feeding parameters^b^	
– Parenteral nutrition intake (mL/kg/day) – Enteral nutrition intake (mL/kg/day) – Total caloric intake (Kcal/kg/day) – Type of milk: human milk or formula – Modality of feeding (bolus, gavage, continuous feeding) – Modality of fortification (if any; type of fortifier: standard, target, or adjustable fortification) – Enteral feeding interruptions (episodes/day) – Not given feeds (episodes/day) – Pathologic gastric residual volumes (episodes/day) – Vomits and/or regurgitations (episodes/day) – Abdominal distention (medium score/day)	
Auxological parameters^c^	
– Weight (g) – Length (cm) – Cranial circumference (cm)	
Overall health status parameters^d^	
– Patent ductus arteriosus – Intraventricular hemorrhage – Leukomalacia – Retinopathy of prematurity – Pneumothorax – Blood transfusion – NEC – Intestinal perforation	

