^a^Ventilation/respiration parameters will be recorded at enrollment, at achievement of half enteral feeding and full enteral feeding, at the beginning of oral feeding, at achievement of full oral feeding, and at any change in respiratory assistance strategy. Apnea monitoring will extend until any respiratory support is needed (except for O_2_ supplementation per nasal cannula)

^b^Feeding parameters will be recorded daily until full enteral feeding is achieved, at the beginning of oral feeding, at achievement of full oral feeding, and at any change in respiratory assistance strategy

^c^Auxological parameters will be recorded at the time of enrollment, upon achieving half enteral feeding and full enteral feeding, and at discharge

^d^Relevant clinical events/diagnosis will be recorded from enrollment until discharge

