### Outcomes

The primary outcome of the study is the time needed to reach FEF, defined as an enteral intake of 150 mL/Kg/day. Secondary outcomes are listed in Table 4.

**Table 4 Tab4:** Secondary outcomes

– Time to reach HEF, defined as an enteral intake of 75 mL/Kg/day (days) – Interruptions of enteral feeding (episodes/day) – Not given feeds (episodes/day) – Pathologic gastric residual volumes (episodes/day) – Vomits and/or regurgitations (episodes/day) – Abdominal distention (mean score/day) – Beginning of oral feeding (post-menstrual age) – Time to reach full oral feeding (number of days) – Post-menstrual age at full oral feeding (weeks) – Weight growth (∆ z-score) – Duration of the respiratory support assigned at randomization (days) – Total duration of respiratory support need (days) – Failure of the respiratory support assigned at randomization (yes/no) – Length of hospital stay (days) – Duration of central venous catheter (days) – Clinical events and complications (NEC, bowel perforation, pneumothorax, BPD, PDA, ROP, IVH, PVL) – Transfers to other hospitals or deaths before reaching full enteral feeding (number of patients)	

*HEF* half enteral feeding, *NEC* necrotizing enterocolitis, *BPD* bronchopulmonary dysplasia, *PDA* patent ductus arteriosus, *ROP* retinopathy of prematurity, *IVH* intraventricular hemorrhage, *PVL* periventricular leukomalacia

The design of the study is outlined in Fig. 1. The Standard Protocol Items: Recommendations for Interventional Trials (SPIRIT) figure of enrollment, interventions, and assessments is shown in Fig. 2. The SPIRIT checklist is provided as Additional file 1.

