### Statistical analysis and sample size

Time to reach FEF, the primary outcome, will be analyzed by Kaplan and Meier survival analysis according to the intention-to-treat principle. The two arms will be compared with the log-rank Test [36].

Regarding secondary outcomes, the time to reach half enteral feeding and time to reach full oral feeding will be estimated by Kaplan and Meier analysis, the failure of the respiratory support assigned at randomization will be compared using Fischer’s exact test, and the other secondary outcomes will be estimated using appropriate generalized linear models. This will be a single-blind trial where the blinded person will be the statistician.

Based on a population of infants with a gestational age < 30 weeks who are consecutively admitted to the NICUs of each research unit from January to June 2017 (mean time of FEF 19.6 days) and considering a ratio between the subjects of the two arms of 1:1, a sample size of at least 141 patients per arm has been calculated to observe a difference of 30% between the two arms (5.7 days).

An interim analysis is planned upon reaching the enrollment of half of the patients expected by the sample size calculation.

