## Discussion

The identification of the most suitable NRS technique for preterm infants with RDS and FI could reduce gastrointestinal complications, improve growth, and reduce hospital stay, thus improving quality of life of infants and their family and reducing health costs.

The evaluation of the timing of oral feeding could be useful in understanding the influence that NRS techniques have on the development of sucking-swallowing coordination.

A standard protocol for the suspension of feeding will be proposed along with a new clinical score to evaluate signs of FI. It may be useful to evaluate the influence, on clinical practice and on the time of achievement of FEF, of the application of a defined and shared method for the evaluation of feeding tolerance. The authors considered a difference of 30% in the time to reach FEF between the groups as the minimum needed to observe a clinically relevant effect. As a consequence, the sample of this study was set at 141 patients per arm.

The evaluation of the response to NCPAP and HHHFNC could clarify their efficacy as treatment for RDS in extremely preterm infants.

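### Every weight after enrolment is taken at an event whose timing is itself a trial outcome, so the change in weight z-score spans an interval that treatment may alter

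*Protocol article*

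**What the plan says.** Footnote c of Table 3 (Methods, Monitoring and data collection) sets the schedule for weight, length and head circumference: "Auxological parameters will be recorded at the time of enrollment, upon achieving half enteral feeding and full enteral feeding, and at discharge". The same section says of the table: "All data recorded throughout the study period are listed in Table 3". No weight at a fixed postnatal or post-menstrual age appears in it.

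The three later events return under Outcomes as end points. On full enteral feeding (FEF): "The primary outcome of the study is the time needed to reach FEF, defined as an enteral intake of 150 mL/Kg/day". Table 4 lists half enteral feeding (HEF) as "Time to reach HEF, defined as an enteral intake of 75 mL/Kg/day (days" and discharge timing as "Length of hospital stay (days".

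The growth outcome in Table 4 reads "Weight growth (∆ z-score" and gives neither a start nor an end point. The Statistical analysis and sample size section places it among the secondary outcomes to be analysed by generalised linear models and names no term for age or interval. The Discussion hopes that the better technique "could reduce gastrointestinal complications, improve growth, and reduce hospital stay".

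**The concern.** A change in z-score is a change over an interval. Here the interval ends when the infant reaches HEF, reaches FEF or goes home, and the trial is set up to find out whether treatment moves those times. If it does, the arms are weighed at different ages on average. Part of any difference in z-score change may then come from when infants were weighed and not from how they grew.

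The direction matters too. If z-scores are falling before FEF, the arm that reaches FEF sooner is weighed after less of the fall and appears to have grown better, which imitates the benefit that the Discussion hopes for. If z-scores are rising, the bias runs the other way.

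At stake is whether this one secondary outcome can be read as an effect on growth.

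**Working it through.** **Step 1. Is each weighing tied to an outcome?**

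| Weighing (footnote c) | Status of its timing (Outcomes, Table 4) |
|---|---|
| Enrolment | Before or at randomisation, not affected by treatment |
| HEF, 75 mL/kg/day | Secondary outcome |
| FEF, 150 mL/kg/day | Primary outcome |
| Discharge | Secondary outcome (length of stay) |

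So every weight after enrolment is tied to one. The inclusion criteria require enteral intake below 75 mL/kg/day, so HEF does come after enrolment.

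**Step 2. The planned shift in timing.** The sample size section gives a "mean time of FEF 19.6 days" and a 30% difference, stated as 5.7 days.

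- 0.30 × 19.6 = 5.88 days.
- 5.7 / 19.6 = 29.1%, and 5.7 / 0.30 = 19.0 days.

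The stated figure is therefore slightly below 30% of 19.6. The gap makes no difference here, and I use 5.7. Under the planned effect, mean time to FEF is 19.6 days in one arm and 19.6 − 5.7 = 13.9 days in the other.

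**Step 3. The artefact when growth is identical.** Let both arms follow one z-score curve f. Enrolment is at t0 (equal on average by randomisation), and FEF is at t1 in the slower arm and t2 in the faster arm.

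- Change, slower arm: f(t1) − f(t0).
- Change, faster arm: f(t2) − f(t0).
- Difference: f(t2) − f(t1). Its size is |slope| × (t1 − t2), where the slope is the average between t2 and t1.

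The documents give no slope, so the values below are assumptions, and they include zero.

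| Assumed slope (z/day, either sign) | × 5.7 days = artefact (z) |
|---|---|
| 0 | 0 |
| 0.01 | 0.06 |
| 0.02 | 0.11 |
| 0.05 | 0.29 |

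**Step 4. Could it be mistaken for an effect?** With n = 141 per arm, as the article states, and a two-sided 5% test, the chance of a significant difference from timing alone is about Φ(artefact / (SD × √(2/141)) − 1.96). The SD of the z-score change is also an assumption. SD 0.5 gives a standard error of 0.060, and SD 0.8 gives 0.095.

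| Slope (z/day) | SD 0.5 | SD 0.8 |
|---|---|---|
| 0 | 5% | 5% |
| 0.01 | 16% | 9% |
| 0.02 | 48% | 22% |
| 0.05 | >99% | 85% |

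**Step 5. HEF and discharge.** The article gives no expected time to HEF and no length of stay, so neither shift can be computed.

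**The case against.** **Z-scores already allow for age.** They do so for the level: an infant weighed at 14 days and one weighed at 20 days are each compared with the right reference. That stands, and different ages alone do not bias the comparison. What it does not cover is a change over unequal intervals. Two conditions are needed for distortion: treatment must shift the timing, and the curve must not be flat over the window.

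**The size is assumed.** This also stands. The article describes no z-score trajectory. The steepest slope used would mean a fall of 0.05 × 19.6 = 0.98 z over the reference time to FEF, for which the document offers no support. Zero belongs in the range.

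**The interval may be fixed elsewhere, or age adjusted for.** The full protocol and analysis plan are not shown, and leaving the model and the interval to them is normal. That is no fault, but it helps only in part. Each end point offered by footnote c is treatment-dependent, so choosing among them does not remove the problem. Adjusting for age at FEF or at discharge conditions on a post-randomisation outcome. A longitudinal model on age could use up to four weights per infant, but at times that the outcomes themselves determine.

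**Other weights may be captured.** A reader might infer that no fixed-age weight exists to repair the comparison. The article does not support that. All data come from the clinical records, which can be expected to hold other weights. Nor is Table 3 literally exhaustive: bronchopulmonary dysplasia and catheter duration are outcomes in Table 4 but are not listed there. What can be said is that the stated schedule includes no such weight.

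**Missing values are not special to this schedule.** Infants who die or are transferred before FEF leave the study without an FEF or discharge weight, but a fixed-age weight could be missing for them as well. An infant who stays and never reaches FEF still has a discharge weight.

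**Conclusion.** The point holds in a conditional form. The schedule that the article states ties every post-enrolment weight to an event whose timing is an outcome, so any z-score change built from it covers an interval that treatment may lengthen or shorten. If the planned 5.7-day effect on FEF is real, the spurious difference in enrolment-to-FEF change is 0 to 0.29 z for assumed slopes of 0 to 0.05 z per day. It is exactly zero if the curve is flat there or if treatment does not move the timing.

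Two stronger readings should be avoided. One is that the growth comparison is certain to be biased and cannot be interpreted; that would need a slope which the document does not give. The other is that the same distortion is established at discharge: the Discussion says only that stay could be shortened, no shift can be computed, and the effect may be small if the curve has levelled off by then.

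Only a secondary outcome is concerned, and the primary analysis and sample size are untouched. Confidence is moderate: firm on the mechanism, weak on the size. The change is worth making because it is cheap.

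**What to change.** 1. In footnote c of Table 3, add a weight at one age common to both arms, taken from the clinical records: for example 36 weeks post-menstrual age, and optionally day 28 as well.
2. In Table 4, define the growth outcome as the change in weight z-score from enrolment to that age.
3. Keep the HEF, FEF and discharge weights as descriptive data.
4. State in advance how infants who die, are transferred or are discharged before the chosen age will be handled.

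The cost is one or two extra data entries per infant and the rule in item 4. No new procedure is needed and clinical care does not change. The fix removes the timing artefact from the growth comparison, but it does not remove missing data, which is why item 4 is needed.

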### Outcomes

The primary outcome of the study is the time needed to reach FEF, defined as an enteral intake of 150 mL/Kg/day. Secondary outcomes are listed in Table 4.

**Table 4 Tab4:** Secondary outcomes

– Time to reach HEF, defined as an enteral intake of 75 mL/Kg/day (days) – Interruptions of enteral feeding (episodes/day) – Not given feeds (episodes/day) – Pathologic gastric residual volumes (episodes/day) – Vomits and/or regurgitations (episodes/day) – Abdominal distention (mean score/day) – Beginning of oral feeding (post-menstrual age) – Time to reach full oral feeding (number of days) – Post-menstrual age at full oral feeding (weeks) – Weight growth (∆ z-score) – Duration of the respiratory support assigned at randomization (days) – Total duration of respiratory support need (days) – Failure of the respiratory support assigned at randomization (yes/no) – Length of hospital stay (days) – Duration of central venous catheter (days) – Clinical events and complications (NEC, bowel perforation, pneumothorax, BPD, PDA, ROP, IVH, PVL) – Transfers to other hospitals or deaths before reaching full enteral feeding (number of patients)	

*HEF* half enteral feeding, *NEC* necrotizing enterocolitis, *BPD* bronchopulmonary dysplasia, *PDA* patent ductus arteriosus, *ROP* retinopathy of prematurity, *IVH* intraventricular hemorrhage, *PVL* periventricular leukomalacia

The design of the study is outlined in Fig. 1. The Standard Protocol Items: Recommendations for Interventional Trials (SPIRIT) figure of enrollment, interventions, and assessments is shown in Fig. 2. The SPIRIT checklist is provided as Additional file 1.

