### Inclusion criteria

All infants admitted to the NICUs with a gestational age between 25 and 29 weeks and who will have met the following inclusion criteria will be consecutively enrolled in the study:Presence of RDSPeriod of stability on HHHFNC or NCPAP for at least 48 h in the first 5 days of life (SatO_2 TC_ 90–95%, pCO_2_ ≤ 60 mmHg, FiO_2_ < 40%, Silverman score [29] ≤ 6, ≤ 2 apnea episodes/h with CPAP ≤7 cmH_2_O if on NCPAP, and flow ≤7 L/min if on HHHFNC)≤ 7 days of lifeSuitability to start enteral feeding (if already started it should be less than 75 mL/Kg/day)Parental written consent

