#### Minimal standard criteria for enteral nutrition

The decision to increase volume of feeds will be up to the clinicians and in accordance with the protocol used in their own NICU; however, a maximum cut-off for feeding progression was set at 30 mL/kg/day [32, 33].

The indications for the interruption of feeding are based on abdominal examination, the occurrence of vomits/regurgitations and cardiorespiratory events, and the evaluation of alvus and gastric residual volumes (evaluated if required by the protocol in use) as detailed in Table 1 [22, 34, 35]. A score system was developed to evaluate abdominal distension (Table 2).

**Table 1 Tab1:** Criteria for the interruption of enteral feeding

	Minor criteria	Major criteria
Physical examination	• Abdominal distension • Visible bowel ansa • Abdominal distension responsive to gastric suction/rectal stimulation	• Dyschromic abdominal wall • Abdominal distension not responsive to gastric detension/rectal stimulation • Painful abdomen
Regurgitations/vomits	• ≤ 2 episodes between 2 feeds or in the previous 3 h (if not fed)	• > 2 episodes between 2 feeds or in the previous 3 h (if not fed) • Bilious vomiting/hematemesis
Gastric residual volumes (GRVs)^a^	• GRV < 100% of previous feed (bilious or with hematic fragments)	• Hematic/fecaloidal GRV • GRV ≥ 100% of previous feed
Alvus	• Mucous stools	• Hematic stools
Cardiorespiratory (CR) events	• ≥ 3 CR events^b^/h	• ≥ 1 extreme CR event^c^
0–1 minor criteria:	- Continue enteral feeding with increments as per protocol (max 30 mL/kg/day)	
2 minor criteria:	- Stop increasing feeds, re-assess prior to the next feed, and evaluate GRV if not done before - If 2 minor criteria in at least 2 consecutive evaluations, consider reducing volume of feed	
1 major criterion or 3 minor criteria:	- Interrupt enteral feeding and re-assess prior to the next feed	

^a^The evaluation of GRVs is elective and according to the protocol of each research unit. GRVs are considered pathological according to minor and major criteria

^b^CR events were defined as episodes of apnea lasting more than 20 s or more than 5 s if followed by desaturation or bradycardia, episodes of desaturation with blood oxygen saturation below 80%, and episodes of bradycardia with heart rate below 80 beats per minute

^c^Extreme CR events were defined as CR events requiring resuscitation

**Table 2 Tab2:** Abdominal distension score

Extent of distension	Score
Abdomen is not distended	0

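### Entry intake may lie anywhere from 0 to just under the 75 mL/kg/day that defines half enteral feeding, yet the stated time-to-HEF analysis does not account for it, so this secondary outcome may lose precision

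*Protocol article*

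**What the plan says.** All of the following is in the protocol article.

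- **Entry.** Under Inclusion criteria, an infant qualifies if suitable to start enteral feeding. If feeding has begun, intake must be below 75 mL/kg/day. Infants at 0 are therefore eligible, and so are infants just short of 75. Entry is early: stability is required "for at least 48 h in the first 5 days of life", and age may not exceed 7 days.
- **Outcomes.** Table 4 gives "Time to reach HEF, defined as an enteral intake of 75 mL/Kg/day (days"). The primary outcome is "the time needed to reach FEF, defined as an enteral intake of 150 mL/Kg/day".
- **Feed progression.** Under Minimal standard criteria for enteral nutrition, "a maximum cut-off for feeding progression was set at 30 mL/kg/day". Within that ceiling, "The decision to increase volume of feeds will be up to the clinicians". At two minor criteria in Table 1 the instruction is "Stop increasing feeds, re-assess prior to the next feed, and evaluate GRV if not done before", and feeding is interrupted at one major or three minor criteria.
- **Allocation.** Under Recruitment and randomization, the software balances gestational age (below 28 weeks against 28 weeks or more) within each unit. Entry intake is not named.
- **Analysis.** Under Statistical analysis and sample size, "the time to reach half enteral feeding and time to reach full oral feeding will be estimated by Kaplan and Meier analysis". No baseline term is mentioned.
- **Data.** Enteral intake is in Table 3, whose footnote says "Feeding parameters will be recorded daily until full enteral feeding is achieved".

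**The concern.** The event threshold for HEF equals the upper entry limit, so infants start the HEF clock at very different distances from the event. One admitted at 70 mL/kg/day has 5 left to go; one admitted unfed has 75. The same number of days to HEF therefore describes different amounts of feeding progress.

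An infant close to the threshold may pass it before the assigned technique has had much time to act. Such infants contribute short, similar times to both arms. Because intake is recorded daily, many of those times will be tied. An unadjusted comparison treats the variation due to starting intake as noise.

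Feeding tolerance is the first aim of the trial, and HEF is its early time-to-event measure. A null HEF result could be read as absence of an effect on early feeding when the comparison was simply insensitive.

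**Working it through.** **Plan's own figure.** The article gives no planning figure for HEF. The 141 per arm belongs to time to FEF and is used below only as the number of infants available.

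**Step 1: distance to the event.** Let e be enteral intake at randomisation, with 0 ≤ e < 75.
- HEF: 75 − e, from 75 down to almost 0.
- FEF: 150 − e, from 150 down to just over 75.

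For FEF the furthest infant has at most twice as far to go as the nearest. For HEF there is no such limit.

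**Step 2: fewest days to the event**, taking time from randomisation (an assumption, since the article does not state the origin), a steady daily increment r and no holds. Days to HEF = ceil((75 − e)/r); days to FEF = ceil((150 − e)/r).

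| e (mL/kg/day) | HEF, r = 10 | HEF, r = 20 | HEF, r = 30 (ceiling) | FEF, r = 30 |
|---|---|---|---|---|
| 0 | 8 | 4 | 3 | 5 |
| 15 | 6 | 3 | 2 | 5 |
| 30 | 5 | 3 | 2 | 4 |
| 45 | 3 | 2 | 1 | 4 |
| 60 | 2 | 1 | 1 | 3 |
| 74 | 1 | 1 | 1 | 3 |

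One increment suffices when e ≥ 75 − r, that is from 45 at the ceiling, 55 at 20 per day and 65 at 10 per day.

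**Step 3: how much of time to HEF entry intake explains.** The article gives neither the entry-intake distribution nor the actual rate of advance, so both are assumed. Daily intake was simulated under three settings: mean increment 20, 10 or 8 mL/kg/day, coefficient of variation 0.3, 0.5 or 0.6, and 10%, 30% or 30% of days without advance. Increments were capped at 30. R² is the share of variance in days explained by e. The last two columns give the standardised difference between arms when one arm advances at 0.7 times the rate.

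| Assumed entry intake | R², HEF | R², FEF | HEF within 1 day | Difference, HEF | Difference, FEF |
|---|---|---|---|---|---|
| Uniform 0–75 | 0.38–0.62 | 0.09–0.26 | 7–23% | 0.46–0.58 | 0.66–1.09 |
| Half at 0, half uniform 0–75 | 0.28–0.55 | 0.08–0.25 | 4–12% | 0.54–0.74 | 0.66–1.14 |
| Uniform 45–75 | 0.33–0.35 | 0.02–0.08 | 19–59% | 0.44–0.51 | 0.68–1.21 |
| Uniform 0–25 | 0.03–0.10 | 0.01–0.02 | 0% | 0.67–1.11 | 0.70–1.30 |

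When all infants enter low, HEF is nearly as sensitive as FEF. When entry intake is spread out or high, HEF falls well behind.

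**Step 4: what adjustment recovers.** Assumptions: 141 per arm; one technique slows progression by 15%; mean increment in the range 15–25, capped at 30; 15% of days with a setback; the stated share enters at 0–10 mL/kg/day and the rest uniformly on 10–75; 400 simulated trials per row.

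| Share entering near zero | Power, arm only | Power, Cox with entry intake | Gain (points) |
|---|---|---|---|
| 20% | 35% | 50% | 15 |
| 50% | 54% | 61% | 7 |
| 80% | 67% | 69% | 2 |

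Each power estimate has a standard error of about sqrt(0.35 × 0.65/400) = 2.4 points, so the last row shows no clear gain. A second set of scenarios, which included slower mean advance of 10–12 mL/kg/day, gave for example 39% against 62% with few infants near zero (gain 23) and 61% against 62% with most near zero (gain 1). The gain thus runs from about nil to about 20 points. That is the spread of the scenarios tried, not a bound.

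**The case against.** **Definitions.** The matching thresholds are coherent. HEF is half of FEF (75 of 150), and capping entry below 75 ensures that nobody enters with the event already reached. This stands in full; the two sections do not contradict each other.

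**Bias.** Randomisation balances entry intake in expectation, and an unadjusted test keeps its type I error. This also stands. What is lost is precision, in one of 17 listed secondary outcomes for which the trial claims no power.

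**Stronger readings.** A reader might infer that infants near the cut-off will cross within a day in either arm, or that time to HEF mostly measures entry intake. The article supports neither. The 30 mL/kg/day figure is a ceiling, increments are the clinician's decision, and feeds can be held or interrupted, which is how intolerance would show. The explained share ranges from about 3% to 62% by assumption, and passes one half only when entry intakes are widely spread and advance is fast.

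**Rate of advance.** The planning mean of 19.6 days to FEF suggests slow progress: 150/19.6 is about 7.7 mL/kg/day from birth, or 150/12.6 about 11.9 if advance from zero began only on day 7. The origin of the 19.6 days is not stated, so this is indicative. At about 12 per day, one-step crossing needs entry at about 63 or above rather than 45. This narrows the group with the shortest times, but the gain from adjustment persisted in scenarios with slower advance.

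**Time origin.** The article does not say when the HEF clock starts. Counting from birth or first feed would spread the times of infants near 75, but part of that time would precede allocation and could not reflect the assigned technique.

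**Level of detail.** Covariates for a secondary outcome are often left to the analysis plan, which is not at hand and may already provide for this. However, the article does name the HEF method, the threshold and the entry limit, and the point concerns how those stated choices combine.

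**Conclusion.** The point holds as one of precision and sensitivity. The article lets infants start at any distance from the HEF event, from 75 mL/kg/day to almost none, then neither balances that distance at allocation nor uses it in the stated analysis. It shows no bias and no inconsistency, and the primary outcome is much less affected.

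The size cannot be fixed from the article. If most infants enter near zero, which the early entry window makes possible, the loss is negligible. If entry intakes are spread across the permitted range, the loss is material. These figures rest on assumed entry distributions, rates of advance and effect sizes, on time counted from randomisation, and on reading the stated HEF analysis as an unadjusted comparison. The case for acting does not need the upper end of the range, because the remedy is nearly free.

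**What to change.** In Statistical analysis and sample size, keep the Kaplan-Meier curves for time to HEF and add three things:

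1. Time to HEF is counted from randomisation.
2. The arms are compared with a Cox model that includes enteral intake at randomisation, or with a log-rank test stratified by bands of that intake fixed before outcomes are examined by arm.
3. The intake used is the value before allocation. It has to be known to check eligibility, and enteral intake is already among the Table 3 data.

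A separate analysis of infants entering below 45 mL/kg/day is not needed. It would add another comparison, and 45 marks one step only at the progression ceiling.

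The cost is a few lines of analysis text and no new data. The one small downside is that the HEF effect becomes conditional on entry intake and should be reported as such.
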